**Tools for use with carer**
*EQ-5D-5L* Carer quality of life will be measured using the EQ-5D-5L detailed above. Carers will also use the EQ-5D-5L to assess the patient’s quality of life.
*Decisional Conflict Scale (DCS)* Carers views on the patient’s Satisfaction with Decision Making will also be explored using the DCS. It will be used with patients and carers at baseline and at 6 months.
*Carer questionnaire* Care-related costs to carers using questionnaires will be captured whilst patient included in study or study end. Cost measures will include caregiver’s lost income and out-of-pocket expenditures for formal care-giving services.
**Renal Clinicians/CNS**
*Qualitative interviews* Individual semi-structured interviews with renal physicians/CNS will focus on the decision making process with patients and carers that precedes referral to conservative kidney management. Experiences of physicians related to counselling a patient who makes the decision not to commence dialysis will be captured (For interview guide based on the Decisional Conflict Scale (DCS) (see Table 3)

#### Carers

At baseline and 3-monthly for 12 months, carers will be asked to complete, the EQ-5D-5L whilst the patient is included in study or 3 months after death of patient or study end; the EQ-5D-5L for the patient by proxy and a questionnaire to measure the subjective and objective burden of providing care, loss of earnings and the opportunity costs of providing care. The DCS will be completed at baseline and 6 monthly (see Table 2).

### Renal physicians/clinical nurse specialists

Exploratory semi-structured qualitative interviews with consultant nephrologists and CNS will be undertaken by the Chief Investigator over the period of the study to explore the decision making process that precedes referral to conservative kidney management in relation to patient satisfaction in decision making. Questions can be viewed in Table 3.

**Table 3 Tab3:** Interview guide for qualitative interviews with renal physicians/clinical nurse specialists

Do you feel your patients know what treatment options are available to them?
Do you think they know the benefits of each option?
Do you think they know the risks and side effects of each option?
Do you think they are clear about which benefits matter most to them?
Do you think they are clear about which risks and side effects matter most to them?
Do you think they are clear about which is more important to them (the benefits or the risks and side effects).
Do you think they have enough support from others to make a choice?
Do you think they choose without pressure from others?
Do you think they have enough advice to make a choice?
Do you think they are clear about the best choice for them?
Do you think they feel sure about what to choose?
Do you think the decision is easy for them to make.
Do you think they feel they make an informed choice?
Do you think their decision shows what is important to them?
Do you expect them to stick with their decision?
Do you think they are satisfied with their decision?
What guidelines/decision tools do you use with your patients when helping them make treatment decisions?

#### Outcome measures

The primary outcome of the study is QOL of patients at 3 months measured using the EQ-VAS.

The range of data collection tools can be viewed in Table 2

### Secondary outcome measures

#### Patients

Changes in QOL, symptoms, anxiety and depression in patients using the Kidney Disease QOL (KDQOL) tool, EQ-5D-5L (which includes the EQ-VAS) and Palliative Outcome Scale - Symptoms (POS-S) Renal 3-monthly over 12 monthsChanges in cognition and frailty status in patients using the 6 Item Cognitive Impairment Test (6CIT) and the 9-point Clinical Frailty Scale 3-monthly over 12 monthsChanges in Performance in patients using the Palliative Performance Scale (PPS) 3-monthly over 12 monthsPatient Satisfaction in Decision Making using the Decisional Conflict Scale (DCS) at baselineMeasurement of health and social care costs of patients receiving conservative kidney management using a Patient Service Use Log 3-monthly over 12 monthsCalculation of the number (%) of patient deaths 3-monthly and time to death.

#### Carers

Carer observation of patient’s Satisfaction in Decision Making using the Decisional Conflict Scale (DCS) at baselineChanges in QOL of carers using the EQ-5D-5L and Carer QOL 3-monthly over 12 monthsCarers assessment of patient QOL using the EQ-5D-5L by proxy 3-monthly over 12 monthsSubjective and objective burden of providing informal care in carers, loss of earnings and the opportunity costs of providing informal care using items from the iMTA Valuation of Informal Care Questionnaire 3 monthly over the 12 months.

### Renal physicians/clinical nurse specialists

Exploration of the decision making process that precedes referral to conservative kidney management in relation to patient satisfaction with renal physicians/CNS via exploratory qualitative interviews.

The range of data collection tools can be viewed in Table 2

#### Quantitative data analysis

Descriptive statistics will be used to summarise baseline demographics and the questionnaire data from patients and carers.

#### Primary outcomes

The mean and 95 % CI for the EQ-VAS will be calculated. Additional exploratory analyses will be used to compare the mean EQ-VAS at 3 months between categories of categorical variables (such as gender, marital status comorbidity) using ANCOVA adjusting for baseline scores. The association between EQ-VAS nd other continuous variables will be investigated using simple linear regression with EQ-VAS at 3 months as the dependent variable. Multiple linear regressions will also be used to investigate associations with comorbidities, age, gender, marital status, severity of symptoms and depression to allow adjustments for confounding. As the study is not powered to detect statistically significant differences in EQ-5D-5L VAS all results will be interpreted with caution. Statistical significance will be assumed for P values 0.05.

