#### Sample size

The primary outcome is to measure the true mean QOL at 3 months using the EQ-5D-5L Visual Analogue Scale (EQ-VAS). The EQ-VAS asks patients to place their health on an interval scale from 0–100 where 0 is the worst state they can imagine and 100 is the best. Using a standard deviation estimate of 18 from a similar study (Nephrol Dial Transplant (2004) 19: 1594–1599),with 100 individuals in our sample we would calculate a 95 % confidence interval for the true mean which would be of width 7.2 units, i.e. 95 % of the time we would estimate the true mean within plus or minus 3.6 units. With an estimated death/dropout rate at 3 months of 10 %, a total of 112 patients are required. For the exploratory qualitative interviews with nephrologists and CNS, in order to achieve data saturation when no new patterns emerge, a sample of approximately 15–20 will be recruited until data saturation reached [39].

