The key contribution of this study will be an assessment of the needs of patients (and carers) managed without dialysis. Findings from this study can lead to development of new healthcare policies and embedded within clinical practice once supportive interventions have been tested and evaluated. Patients will benefit as more accurate information on conservative kidney management, including the predicted QOL without dialysis, can be provided in the counselling process as patients make treatment decisions. Impact on carers will be acknowledged as a first step in developing a health-improvement programme for carers of this patient group. Associated costs of conservative kidney management will be identified allowing for comparison with other ESKD treatment modalities. In the proposed project, knowledge transfer to a broader audience will be facilitated by various mechanisms including carer and user organisations and clinically based staff. The protocol has been developed with clinicians, users and carers with a key benefit of strengthening links between researchers, practitioners, policy makers and voluntary sectors to ensure new knowledge is translated into practice. These links will be developed and utilised to disseminate the results of the proposed programme of research, to raise awareness of developments and research priorities in renal care and end-of-life practice.

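### The plan does not say whose mean EQ-VAS the primary estimate refers to, and enrolling 112 protects the interval's width but not its centre

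*Protocol article*

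**What the plan says.** All references are to the protocol article.

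- **Target (Sample size).** "The primary outcome is to measure the true mean QOL at 3 months using the EQ-5D-5L Visual Analogue Scale (EQ-VAS"). The section does not say whether patients who die before 3 months belong to the population whose mean is meant.
- **Precision (Sample size).** "Using a standard deviation estimate of 18 from a similar study", and "with 100 individuals in our sample", the plan expects a 95% "confidence interval for the true mean which would be of width 7.2 units", and adds that 95% of the time "we would estimate the true mean within plus or minus 3.6 units".
- **Loss (Sample size).** "With an estimated death/dropout rate at 3 months of" 10%, enrolment is set at 112. Death and dropout form one figure, with no split.
- **Analysis (Primary outcomes, under Quantitative data analysis).** The mean and 95% "CI for the EQ-VAS will be calculated". Baseline scores enter only the exploratory ANCOVA comparisons, not the primary mean.
- **Deaths (Secondary outcomes).** Deaths at 3, 6, 9 and 12 months are tabulated and time to death is analysed, as secondary outcomes not linked to the primary mean.
- **Intended use (Discussion).** More accurate information, "including the predicted QOL without dialysis, can be provided in the counselling process", is named as a benefit to patients.

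**The concern.** Raising enrolment to offset losses keeps the standard error where it was planned. It cannot correct the estimate if those lost differ from those who answer.

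The article itself gives grounds to expect a difference. Its ethics section says that some participants will be near death and that assessments will be cut short when patients tire. Table 2 describes the frailty and performance scales as related to the risk of death or to survival. Illness is therefore a likely cause of a missing 3-month score.

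Pooling death with dropout adds a second problem. A living patient who does not answer has an EQ-VAS value that was not recorded. A patient who has died has none. The two losses need different treatment, and which treatment is right depends on whose mean is being estimated.

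The 3.6-unit statement is made about the true mean. Without a named population and an assumption about losses, it says more than the calculation behind it. A clinician or patient could not tell that the figure is conditional on being alive and able to answer.

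**Working it through.** **Inputs from the article:** SD 18; 100 analysed; 10% pooled loss; 112 enrolled; a median of 2.5 remaining life years, which the Background gives for people over 75 with advanced chronic kidney disease.

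**Inputs assumed, not in the article:** living non-completers score 15 to 20 units below completers; survival is exponential; the Background median applies to this cohort.

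**1. Reproduce the plan's figures.**
- SE = 18/√100 = 1.8.
- Half-width: 1.96 × 1.8 = 3.53; with t on 99 df, 1.984 × 1.8 = 3.57; with a multiplier of 2, 3.60. The stated 3.6 (width 7.2) is reproduced.
- Enrolment: 100/0.9 = 111.1, so 112; 112 × 0.9 = 100.8 analysed. This is reproduced too.

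**2. Effect of selective loss.**
- Bias of the completer mean = (fraction missing from the target population) × (completer mean − mean of the missing).
- Coverage of the nominal 95% interval = Φ(1.984 − b/1.8) − Φ(−1.984 − b/1.8), where b is the bias.

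**3. Case A: all 10% are living non-completers.**
- Gap 15: b = 0.10 × 15 = 1.5; coverage 87.3%.
- Gap 20: b = 0.10 × 20 = 2.0; coverage 80.8%.
- With 1.96 in place of 1.984 the coverages are 86.7% and 80.1%, so the choice of multiplier hardly matters.

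**4. Case B: most losses are deaths and the target is patients alive at 3 months.**
- Dead by 3 months: 1 − exp(−ln 2 × 0.25/2.5) = 0.067.
- Missing among the living: 1 − 0.9/0.933 = 0.035.
- Bias: 0.035 × 15 = 0.5 to 0.035 × 20 = 0.7. At b = 0.6, coverage is 94.0%.

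| Case | Missing fraction of target | Assumed gap | Bias | Coverage |
|---|---|---|---|---|
| No difference | any | 0 | 0 | 95% |
| B, mostly deaths | 3.5% | 15 to 20 | 0.5 to 0.7 | about 94% |
| A, all living | 10% | 15 to 20 | 1.5 to 2.0 | 87% to 81% |

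**5. Scale check.** At 10% missing, bias alone equals the 3.6 half-width only if the gap is 3.6/0.10 = 36 units, or two SDs.

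**The case against.** The strongest reply has five parts.

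- **The analysis sentence does not say complete cases.** Methods for missing data are commonly left to an analysis plan, which is not shown. This stands to the extent that the absence of an imputation method is not itself the fault. But the sample-size section counts 100 analysed out of 112, and the primary analysis is a plain mean, so a completer mean follows from what is written. The target population and the meaning of the 3.6 figure belong with the primary outcome.
- **No data show bias.** This stands. The article gives neither a gap between completers and non-completers nor a split of the 10%. A reader might infer that the interval is centred on healthier patients and fails to deliver 3.6 units. The document supports only that this is likely in direction and unknown in size.
- **Deaths are already reported.** This stands. Three-month mortality is a planned secondary result and is not hidden; it is only not tied to the primary mean.
- **Non-response is reduced by design.** This stands in part. Patients may be helped by nurses or carers and the mode is recorded, which should lower the living non-completer fraction but cannot be assumed to remove it.
- **Proxy scores are limited.** This stands. Carers take part only if they opt in, so proxy EQ-5D-5L will exist for a subset.

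The counselling sentence is a general aim of the whole study. It does not present the 3-month mean as the number to quote.

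**Conclusion.** The concern holds in a limited form. As written, the plan yields a completer mean, leaves its target population open, and guards against loss only in interval width. The 3.6 figure is right as sampling precision. As a statement about the true mean, it also needs losses to be ignorable, or the target to be restricted to the patients observed.

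The likely upward bias is modest: about 0.5 to 0.7 units with coverage near 94% if most losses are deaths, and 1.5 to 2.0 units with coverage of 87% to 81% if none are. Both ranges rest on the assumed 15 to 20 unit gap. The first also borrows a median survival from a related but different population and an exponential curve.

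A reader might infer a larger error by scoring deaths at zero: with an assumed mean of 60, that lowers the figure by 60 × 0.067 = 4.0 to 60 × 0.10 = 6.0 units, more than the half-width. The document does not support calling this bias. It defines zero on EQ-VAS as the worst state the patient can imagine, not death, and among patients alive at 3 months the exclusion of deaths causes no bias. The comparison shows only that the choice of target matters and should be stated.

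This should be fixed, but it does not invalidate the primary result.

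**What to change.** 1. Define the primary quantity as mean EQ-VAS at 3 months among patients alive at 3 months, and state the expected deaths and the expected non-completion among the living separately.
2. Estimate it with a mixed model or multiple imputation for living non-completers, using baseline EQ-VAS, Palliative Performance Scale and Clinical Frailty Scale. Baseline values are preferable, because the 3-month ratings come from the same visit and may be missing for the same patients. Add carer proxy EQ-VAS only where a carer has opted in. Do not impute scores for patients who have died.
3. Keep the completer mean as a supportive analysis.
4. Report the primary mean beside the 3-month mortality proportion that is already planned.
5. Describe 3.6 units as sampling precision that assumes ignorable loss.

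**Cost.** Some added wording and analysis work, and possibly a slightly wider interval. The baseline measures are already in the schedule of assessments, so no new data collection is needed and enrolment stays at 112.

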#### Secondary outcomes

Descriptive summaries of patient and carer questionnaire data at 3, 6, 9 and 12 months will be tabulated and presented graphically where appropriate. The number (%) of deaths at 3, 6, 9 and 12 months will be tabulated. Time to death data will be investigated using Kaplan Meier curves. The log rank test statistic will be used to compare categorical variables and Cox proportional hazards model for continuous variables where appropriate.

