
Prospective, randomised trials of dialysis versus conservative kidney management for ESKD are neither ethically justifiable nor practical and therefore only observational studies are available to inform practice [31]. A recent study by Da Silva-Gane and colleagues [32] attempted to compare QOL in patients with advanced chronic kidney disease in those opting for dialysis versus conservative kidney management. This small study, did not investigate clinical decision making, resource use or impact of conservative kidney management on carers. The authors concluded that those opting for conservative kidney management may maintain a better QOL compared to dialysis but higher levels of anxiety were seen in the conservative kidney management patients. The study was limited by major demographic and clinical differences between individuals and the modality groups.

To facilitate improved decision making for individuals with ESKD, accurate information is required for a number of issues including the expected QOL for patients with ESKD, the potential impact a decision not to dialyse may have on the QOL of carers; resource use and costs of conservative care for ESKD and the factors that influence decision making from a patient/carer and health care practitioner perspective [33–36]. Unfortunately there is a dearth of research in this area. The present multicentre study is designed to capture patient and carer profiles when conservative kidney management is implemented and to understand the trajectories of care-receiving and care-giving. It will explore the interactions that lead to clinical care decisions and the impact of these decisions on carers with the intention of improving clinical outcomes for patients and the care giver experience. The economic analysis of conservative kidney management will facilitate greater transparency in relation to resource allocation processes for persons with chronic kidney disease. The purpose of this article is to describe the design of the present study and inform others on the possibilities of performing end-of-life care research in advanced chronic kidney disease. The prospective and longitudinal nature of the design will be discussed. In addition the explanation of the methodology will serve as a comprehensive orientation for the methods section of publications arising from the research.

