The aim of the study is to measure and describe longitudinally QOL, symptoms, cognition, frailty and performance in persons with ESKD being managed without dialysis and the impact of these issues on their carers. In addition, the study will analyse decision making related to conservative care for ESKD together with the costs of conservative kidney management.

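### The patient secondary outcomes are changes over 12 months, but the stated analysis is a summary at each visit, which does not estimate change and can understate decline

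*Protocol article*

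**What the plan says.** The aim, at the end of the Background, is longitudinal: "The aim of the study is to measure and describe longitudinally QOL, symptoms, cognition, frailty and performance". The Background also gives as a purpose "to understand the trajectories of care-receiving and care-giving". Under Secondary outcome measures, Patients, the first three outcomes are worded as changes, each 3-monthly over 12 months:

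- "Changes in QOL, symptoms, anxiety and depression in patients using the Kidney Disease QOL (KDQOL) tool", with the EQ-5D-5L and POS-S Renal;
- cognition (6CIT) and frailty (Clinical Frailty Scale);
- performance (PPS).

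Table 1 schedules all of these at baseline and at 3, 6, 9 and 12 months, so each patient can contribute up to five measurements.

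Under Quantitative data analysis, the Secondary outcomes paragraph gives this for the questionnaire data: "Descriptive summaries of patient and carer questionnaire data at 3, 6, 9 and 12 months will be tabulated and presented graphically where appropriate". It then tabulates deaths at the same four visits, and adds "Time to death data will be investigated using Kaplan Meier curves". An introductory sentence also promises descriptive statistics for baseline demographics and questionnaire data.

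The primary outcome is separate and is not a change: "The primary outcome of the study is QOL of patients at 3 months measured using the EQ-VAS".

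For carers, Data collection describes completing "the EQ-5D-5L whilst the patient is included in study or 3 months after death of patient or study end". The analysis paragraph does not say how carer data from after a death are grouped.

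**The concern.** A column of 12-month scores can hold only patients still alive and responding. If patients with low or falling scores are lost first, the 12-month mean is raised by their absence, and comparing it with the baseline mean does not give the change that the outcome names.

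For two outcomes the selection follows from the article's own text. Table 2 says that the Clinical Frailty Scale predicts death better than measures of cognition, function or comorbidity, and that the PPS correlates well with survival. For EQ-VAS and the other scores the link is plausible, but the article does not state it.

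What is at stake is how the results will be used. The Discussion expects them to inform counselling on the quality of life to be expected without dialysis, and the Economic evaluation section expects comparison with published dialysis estimates. An understated decline would mislead in both uses.

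**Working it through.** **1. The plan's own figures.** SD 18, n = 100 (Sample size). CI width = 2 × multiplier × 18/√100. With multiplier 2 the width is 7.2, as stated; with z it is 7.06 and with t on 99 df it is 7.14. Inflation: 100/0.9 = 111.1, rounded up to 112. These figures reproduce and are not in dispute.

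**2. Patients left at each visit.** The article gives a loss rate only for 3 months (10%, death and dropout together). Two projections, both assumptions:

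| | 3 m | 6 m | 9 m | 12 m |
|---|---|---|---|---|
| 10% per quarter throughout: 112 × 0.9^k | 100.8 | 90.7 | 81.6 | 73.5 |
| Deaths only, exponential, median 2.5 years (Background figure for over-75s): 112 × 0.5^(t/2.5) | 104.5 | 97.5 | 91.0 | 84.9 |

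The loss by 12 months is about 34% or 24%.

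**3. Effect on a difference of visit means.** Inputs assumed, because the article does not give them: baseline EQ-VAS 60; between-patient SD 13 and residual SD 12.4 (total √(13² + 12.4²) = 18.0, matching the article's SD); SD of individual slopes 10 points per year; retention correlated ρ with the patient's level and, separately, ρ with the slope.

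If a fraction p is retained by truncating a standard normal variable, the mean of that variable among those retained is m = φ(c)/p, where c is the (1 − p) quantile. For p = 0.656, m = 0.368/0.656 = 0.561. For p = 0.758, m = 0.3123/0.758 = 0.412.

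Apparent 12-month change = true change + 13ρm (level selection) + 10ρm (slope selection).

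Simulation with 400,000 patients per scenario agrees with this formula to about 0.1. Simulated results:

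| ρ | True −5, 34% lost | True −10, 34% lost | True −5, 24% lost |
|---|---|---|---|
| 0 | −5.0 | −10.0 | −4.9 |
| 0.2 | −2.4 | −7.4 | −3.1 |
| 0.3 | −1.2 | −6.2 | −2.2 |
| 0.5 | +1.4 | −3.6 | −0.2 |

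At 34% loss the share of the decline concealed runs from 0% to more than 100% of a 5-point fall, and from 0% to 64% of a 10-point fall.

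**4. What within-patient change recovers.** Change among patients measured at both times removes the level term and leaves only 10ρm. At 34% loss with true change −5, the simulated values are −3.9, −3.4 and −2.2 for ρ = 0.2, 0.3 and 0.5. That is nearer the truth than the visit means, but not free of selection on slope.

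**5. The 3-month primary outcome.** With p = 0.9, m = 0.1755/0.9 = 0.195. The shift in the mean is (13 + 10 × 0.25) × ρ × 0.195 = 15.5 × ρ × 0.195, which is 0.6, 0.9 and 1.5 points for ρ = 0.2, 0.3 and 0.5. The planned half-width is 3.6.

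**The case against.** The strongest reply is that this is a journal article. Change scores, repeated-measures models, analysis sets and the handling of deaths are often left to a statistical analysis plan, which is not shown. Descriptive summaries could include change from baseline, and the stated aim is itself to describe. That stands in part: the absence of model detail is not the point here. But the article names its methods elsewhere (baseline-adjusted ANCOVA and regression at 3 months; log-rank and Cox for death; multiple regression for costs), while for the repeated scores it names summaries by visit. Followed as written, those do not deliver the outcomes as worded.

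Other parts of the reply stand in full:

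- Deaths are tabulated at the same visits, so part of the changing denominator will be visible. Loss for other reasons is not mentioned there.
- A mean among those alive is a legitimate description if labelled as such. The benchmark in the working counts 12-month scores for everyone lost, and those who died have none.
- A mixed model fitted without regard to death implicitly extrapolates past it. Joint or pattern-mixture models for every instrument in about 112 patients are a matter of preference.

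A reader might infer three stronger things, none of which the article supports. The first is that real decline will be hidden: the link between attrition and the scores is not given, and with no link there is no bias. The second is that the main result is compromised: the primary outcome is a 3-month mean with 10% expected loss. The third is that bereaved and active carers will be pooled: the text is silent on grouping.

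**Conclusion.** The point holds as a mismatch between how the patient secondary outcomes are defined and the analysis stated for them. Differences between visit summaries do not estimate within-patient change and can understate decline, chiefly at 6 to 12 months. For frailty and PPS the direction of selection follows from the article's own account of those scales; for EQ-VAS it is an assumption.

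The size cannot be fixed from the article. It is zero if attrition is unrelated to the score. Under a moderate link (ρ = 0.3), a 5-point fall would appear as about 1 to 2 points across the two retention assumptions. These figures also rest on the assumed variance split and slope SD. The need for the correction does not depend on any particular value.

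**What to change.** In the Secondary outcomes paragraph of Quantitative data analysis, add text to this effect:

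- For EQ-VAS, KDQOL, POS-S Renal, 6CIT, Clinical Frailty Scale and PPS, change from baseline will be estimated within patients, with 95% CIs, from a repeated-measures mixed model using all available visits including baseline. Results will be interpreted as change while alive, not as scores attributed to patients who have died.
- Visit summaries will be kept as description, each shown beside the numbers alive, dead and missing.
- Mean profiles by time of death or dropout will be plotted as a simple sensitivity display, since within-patient change does not remove selection on slope.
- Carer data collected after the patient's death will be labelled and tabulated separately.

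A joint or pattern-mixture model linked to death is optional. If the unseen analysis plan already contains these elements, a sentence in the article pointing to it would suffice. The cost is wording and a modest amount of extra analysis; no new data are needed.
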